### Parent/carers

Inclusion criteria

The inclusion criteria for parents/carers:

1. Is a parent/legal guardian of the CYP
2. Is a UK resident

Exclusion criteria

The exclusion criteria for parents/carers:

1. Does not speak/understand English sufficiently well to access the measures and intervention materials. This is primarily due to limited funding capacities for interpreters
2. Has an intellectual disability at a level meaning that they cannot access the measures and/or intervention. This will not be defined by IQ, but by clinical judgement. Parents/carers will not be excluded because of the presence of intellectual disability per se, but because of being unable to access the materials

## Procedure

### Recruitment and informed consent of participants

Specialist child and adolescent eating disorder services in the UK have been identified as research sites for this project. [name] will obtain honorary contracts at each research site for research activity.

CYP, and their parents/carers, will be contacted by a member of their clinical care team at the site in question. The member of the patient’s clinical care team will provide an overview of the study and will ask families if they would like to receive the study information (i.e., participant information sheet).

If the family agree to receive a participant information sheet, the member of the clinical team will provide this to the family (either electronically or in a paper copy). The information sheet will contain the contact details of the research team so that the CYP, and/or their parents/carers, can contact the research team to ask any questions they may have. The information sheet will also contain a QR code to an online form that potential participants can fill in to share their contact details with the research team to enable the research team to contact them directly.

The member of the clinical team will also ask families for explicit written or verbal consent for their contact details to be held by the research team going forwards. The member of the clinical team will sign a ‘consent to be contacted by the research team’ form to confirm whether written or verbal consent has been obtained by the family for their contact details to be held by the research team.

After a reasonable period of time, the family will be contacted by the study researcher and asked if they have any questions about the study and/or are interested in taking part. Once they have decided to take part, the researcher will gain informed consent/assent via an online consent/assent form. Parents/carers and CYP (aged ≥ 16) will be asked to provide informed consent to participate in the study, and CYP (aged < 16) will be asked to provide assent, in addition to the consent of their parent/carer.

All CYP, and their parents/carers, who start the treatment will be asked by the study researcher if they would like to take part in an optional qualitative interview to explore their experiences and views of the treatment approach. CYP, and their parents/carers, will be able to ask the study researcher any questions they may have. If they are interested in taking part, they will be asked to complete an online consent/assent form.

### Screening and eligibility assessment

Once families have been recruited through one of the recruitment sites, and have completed the study consent/assent forms, their eligibility for the research will be confirmed.

Families who consent/assent to participate in the study will be asked to complete a short screening questionnaire to determine their eligibility for participation (see [Appendix 1](#Appendix1)). This will include demographic information about the CYP and their parent(s)/carer(s), confirmation of UK residency, information about prescribed psychotropic medication of the CYP, current/previous psychological support received by the CYP, brief questions to determine if the CYP is experiencing possible symptoms of eating disorders that impair their functioning and a question around current self-harm and suicidality. This questionnaire can be completed online or via telephone with the study researcher. It is expected that this questionnaire will take approximately 15 minutes to complete. If families are not eligible for the study, the study researcher will contact the family to explain why they are not eligible for the research, and signpost them to relevant support, as necessary. If the screening questionnaire indicates that the family meet the eligibility criteria, they will be invited to enrol in the study.

### Procedure once participants are enrolled

Once participants are enrolled into the study, CYP and their parents/carers will be invited to complete the baseline measures, including a battery of questionnaires, including the self-report of the Eating Disorder Examination Questionnaire [EDE-Q] and the parent-report of Eating Disorder Examination Questionnaire [PEDE-Q]). This is to confirm that the intervention is appropriate (i.e., that the CYP has impairing symptoms of eating disorders and an absence of significant risk as detailed in the inclusion/exclusion criteria). Families may also be asked to complete the online Development and Wellbeing Assessment (DAWBA) to enable an understanding of comorbid diagnoses. Note – the DAWBA will be piloted with families in the first instance. If the family have already completed the DAWBA during their assessment with the eating disorder service, this data will be accessed to prevent duplication of measures. Following the pilot, it may be decided to no longer use the DAWBA, and families will be asked to complete the Strengths and Difficulties Questionnaire (SDQ) at baseline instead.

Questionnaires will be sent to families to complete online (or over the telephone if preferred). The questionnaires will cover some additional demographic information about the family ([Appendix 2](#Appendix2)), brief questions about the CYP’s eating disorder symptoms and how they impair their functioning, and symptoms of anxiety and depression. They will also be asked to report on the CYP’s current weight and height. It is expected that these questionnaires will take approximately 15 minutes to complete. Families may also complete the DAWBA online (or over the telephone with a researcher if preferred) which will take around 45 minutes to complete.

Families will then be invited to attend a feedback appointment where the study researcher will feed back the information obtained from the questionnaires, and to discuss next steps regarding the intervention. This feedback appointment is likely to last around 30 minutes. The family will be given a report summarising the outcomes of the questionnaires and the next steps for treatment. The family’s GP and other teams involved in their care (e.g., eating disorder service) will also be sent a copy of this report to inform them about the family’s participation in the study.

Families will commence treatment up to one week after completing the baseline measures (depending on how soon they can attend their first guidance session). Families will be given access to a website and interactive PDFs, and will receive 8 individual guidance sessions via a videocall or over the telephone with a Guide. They will be asked to complete weekly questionnaires throughout the intervention to assess week-to-week changes. These weekly questionnaires will take around 15 minutes to complete each week.

CYP and their parents/carers will be asked to complete the post-treatment measures 12 weeks after completing the baseline measures. This involves reporting on the CYP’s current weight for height, completing a brief questionnaire about the CYP’s symptoms of eating disorder, anxiety and depression, and emotional and behavioural difficulties. It will also involve a questionnaire to assess the acceptability of the treatment approach. It is anticipated that these questionnaires will take approximately 30 minutes to complete.

Families will then be invited to attend a feedback appointment to review the outcomes of these post-treatment measures, and to signpost them to further support if required. This appointment is expected to be around 30 minutes in duration.

CYP, and their parents/carers, will also be invited to attend an optional qualitative interview to explore their experiences of the intervention. It is anticipated that this interview will last approximately 45 minutes.

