| Baseline and outcome measures | Baseline and post-intervention measures:   - Eating Disorder Examination Questionnaire self-report (EDE-Q) and parent-report (PEDE-Q) - Clinical Impairment Assessment (CIA) - %Weight-for-height - Revised Child Anxiety and Depression Scale (RCADS) - DAWBA (baseline only) or SDQ (total and impact supplement)   Session-by-session measures:   - Eating Disorder-15 for Youth (ED-15-Y) - Goal Based Outcomes (GBOs) - Outcome Rating Scale (ORS)/Child Outcome Rating Scale (CORS) - SDQ Session-by-session (SDQ SxS)   Post-intervention measures only:   - Acceptability questionnaire - Optional qualitative interview |
| Treatment period | 3 months maximum |
| End of study | The final post-intervention assessment (12 weeks after baseline measures) for the final participant or the last qualitative interview with the final participant, whichever occurs last |

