## Measures

Screening measures

Families will be asked to complete initial screening questions to determine their eligibility for the research and to describe the study sample. This will include demographic information about the CYP and their parent(s)/carer(s), confirmation of UK residency, information about prescribed psychotropic medication of the CYP and current/previous psychological support received by the CYP. They will also be asked to complete a brief questionnaire to determine if the CYP is experiencing possible symptoms of eating disorders (i.e., the Child Eating Disorder Examination Questionnaire – 8-items; ChEDE-Q8), as well as some questions regarding the extent to which these eating disorder symptoms impair functioning (adapted from the Strengths and Difficulties Questionnaire (SDQ) impact supplement) and a question around current risk (see [Appendix 1](#Appendix1)).

*Child Eating Disorder Examination Questionnaire – 8-items (ChEDE-Q8; Kliem et al., 2017)*

The ChEDE-Q8 is an 8-item self-report measure that evaluates four areas of eating disorder psychopathology: restraint, eating concern, shape concern and weight concern. The ChEDE-Q8 scores range from 0 (absence of the feature) to 6 (feature present every day to an extreme degree). Global mean scores will be calculated, with higher scores indicating higher levels of eating disorder psychopathology. The ChEDE-Q8 has been validated for children aged ≥ 7 years and has been shown to have strict measurement invariance, internal consistence as well as convergent and factorial validity (Kliem et al., 2017).

Baseline only measures

Psychiatric diagnoses

*The Development and Wellbeing Assessment (DAWBA;* Goodman et al., 2000)

This standardised diagnostic instrument is designed to generate ICD-10 and DSM 5 psychiatric diagnoses. The DAWBA provides a probability of the likelihood of a range of mental health disorders. The DAWBA incorporates the Strengths and Difficulties Questionnaire (SDQ), a brief (25-item) emotional and behavioural questionnaire and its impact supplement (Goodman, 1997). The DAWBA (Brøndbo et al., 2012) has been shown to have excellent reliability and validity.

Baseline and post-intervention measures

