The CIA is a 16-item, self-report questionnaire designed to measure psychosocial impairment due to eating disorder features in the past 28 days. Items are rated on a 4-point Likert-like scale, ranging from 0 (not at all) to 3 (a lot). The 16 items cover impairment in domains of life that are typically affected by eating disorder psychopathology: mood and self-perception, cognitive functioning, interpersonal functioning and work performance. A CIA global score is calculated as a severity index (ranging from 0 to 48), which higher scores indicating greater severity of clinical impairment. The CIA has demonstrated high levels of internal consistency, test-retest reliability, sensitivity to change, construct validity, and discriminant validity (Bohn et al., 2008; Reas et al., 2010). The CIA has been slightly modified to make it applicable to CYP (e.g., item 4 asks about school performance as opposed to work performance).

%Weight-for-height

CYP, and their parents/carers, will be asked to report on the CYP’s body weight and height so that their %weight-for-height (Weight x 100 reference weight for CYP of the same height) can be calculated.

Depression and anxiety symptomatology

*The Revised Child Anxiety and Depression Scale (RCADS; Chorpita et al., 2000)*

The self-report and parent-report versions of the RCADS will be used to measure the CYP’s anxiety and depression symptoms. It is a 47-item questionnaire for 8-18 year olds, which is sub-divided into six scales: separation anxiety disorder, social phobia, generalised anxiety disorder, panic disorder, obsessive compulsive disorder and low mood (major depression). Each item is scored on a 4-point Likert scale from 0 (never) to 3 (always). In addition to the subscales, the RCADS can be used to calculate a total anxiety score and total anxiety and depression score. The RCADS has good reliability on subscales and total scale, with internal consistency of adequate to excellent across the different subscales (Chorpita et al., 2005). The measure also has good test-retest reliability, and good convergent and concurrent validity (Chorpita et al., 2005; Donnelly et al., 2019).

If it is decided to no longer use the DAWBA following the pilot, families will be asked to complete the Strengths and Difficulties Questionnaire (SDQ) instead.

*The Strengths and Difficulties Questionnaire (SDQ; Goodman, 1997)*

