The ORS/CORS is a four-item scale that assesses areas of life functioning that change in response to therapeutic intervention: symptom distress, interpersonal wellbeing, social life, and overall wellbeing. Each dimension is displayed as a visual analogue scale ranging from 0 to 10 (10 = better functioning). The ORS is designed for children aged 13-18 years and the CORS can be completed by children aged 6-12 years; the CORS has the same format but contains more child friendly language and smiley and frowning faces. The ORS/CORS has good concurrent validity with other outcome measures, and high internal consistency and test-retest reliability (Duncan et al., 2006).

*Strengths and Difficulties Questionnaire Session by Session (SDS SxS; Hall et al., 2015)*

The SDQ SxS measure is a modified form of the SDQ Impact Supplement that is intended for intervention progress monitoring. Self-rated items assess young people’s improvement, impact of problems on everyday life in the present and anticipated improvement in the future.

CYP will be asked to provide their weight every week for risk and medical monitoring.

Post-treatment only measures

*The Strengths and Difficulties Questionnaire (SDQ; Goodman, 1997)*

The self-report and parent-report versions of the SDQ will be used to assess the CYP’s psychological wellbeing. The SDQ is brief (25-item) emotional and behavioural questionnaire for CYP aged 2-17 years of age. The 25 items comprise 5 scales of 5 items each, each rated on a 3-point Likert scale ranging from 0 (‘not at all’) to 2 (‘certainly true’). The scales include: emotional symptoms, conduct problems, hyperactivity/inattention, peer relationship problems, prosocial behaviour. The first four subscales can be summed to provide a total difficulties score. The SDQ also has an ‘impact supplement’ which assesses the functional impairment of the identified problems across four domains (school, home, friendships, leisure). Impact items are scored on a four-point scale from 0 (‘not at all’) to 2 (‘a great deal’). The reliability and validity of the SDQ has been established (Goodman, 2001; Muris et al., 2003).

*Acceptability questionnaire*

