## Data analysis

### Quantitative analysis

Statistical analyses will be performed using IBM SPSS Statistics 27. Descriptive analyses will be used to characterise the sample, to examine the participant flow through the study and attrition rates at each stage, and to assess satisfaction with the intervention.

Baseline and post-intervention measures

Symptom change will be measured by comparing scores at baseline and end of treatment. In order to ensure that the outcomes are not affected by attrition, the analyses will be conducted using Intention to Treat methods. Paired t-tests will be used to compare differences from the baseline measures to end of treatment, and Cohen’s *d* will be used to determine effect sizes (small effect ≥ 0.2, medium effect ≥ 0.5 and large effect ≥ 0.8).

Outcomes will also be evaluated on an individual level using Jacobson and Truax (1991)’s indices of meaningful change: Reliable Change Index (RCI) and Clinically Significant Change (CSC). Achievement of RCI indicates that the observed change is unlikely to be due to measurement error, and achievement of CSC indicates that change is substantial, relative to the clinical and non-clinical ranges of scores.

Session-by-session measures

Weekly measures (ED-15-Y, GBOs, ORS/CORS and SDQ SxS) will be analysed visually.

Acceptability

The feasibility and acceptability of the guided self-help intervention will be evaluated by analysing the treatment satisfaction of participants using both questionnaire measures and qualitative interviews.

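### Families whose clinic DAWBA is reused have no SDQ dated at study baseline, so their SDQ change either includes pre-study time or cannot be computed

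*Protocol*

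**What the plan says.** All references are to the protocol.

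- **Reuse.** *Procedure once participants are enrolled* states: "If the family have already completed the DAWBA during their assessment with the eating disorder service, this data will be accessed to prevent duplication". It sets no maximum age for the clinic DAWBA and asks for no new SDQ in its place. The purpose given for the DAWBA is to understand comorbid diagnoses.
- **Content.** *Measures*, under the baseline-only measures: "The DAWBA incorporates the Strengths and Difficulties Questionnaire (SDQ), a brief (25-item) emotional and behavioural questionnaire and its impact supplement".
- **Stand-alone baseline SDQ.** This is conditional. After the RCADS description, *Measures* says: "If it is decided to no longer use the DAWBA following the pilot, families will be asked to complete the Strengths and Difficulties Questionnaire (SDQ)" in its place. *Procedure once participants are enrolled* says the same.
- **Post-treatment SDQ.** The self- and parent-report SDQ appears under the heading "Post-treatment only measures".
- **Summary table.** Among the baseline and post-intervention measures, the *Study summary* lists "DAWBA (baseline only) or SDQ (total and impact supplement").
- **Timing.** *Procedure once participants are enrolled* puts the post-treatment measures 12 weeks after baseline and the start of treatment at most one week after baseline.
- **Analysis.** *Quantitative analysis*: "Symptom change will be measured by comparing scores at baseline and end of treatment", by paired t-test and Cohen's d, with reliable and clinically significant change for individuals.

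**The concern.** A pre-post comparison needs a first measurement taken at the same defined point for everyone. Here the date of the SDQ depends on whether the family's service happened to use the DAWBA. Families without an earlier DAWBA give an SDQ at study entry. Families with one give it at their service assessment, whenever that was.

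The study has no control group and about 10 families. Any change between service assessment and study entry, in either direction, cannot be separated from change during the intervention, and a few families can move the mean. This is also a gap in data collection. An analysis plan can define which SDQ is paired with which, but it cannot supply a baseline SDQ that was not collected before treatment.

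**Working it through.** There is no sample size, power or alpha figure to reproduce on this point. The check is of the measurement schedule, followed by an illustration.

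**Where each family's full baseline SDQ comes from**

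| Situation | Source of baseline SDQ | Date |
| --- | --- | --- |
| DAWBA kept, completed new for the study | Inside the new DAWBA | Study baseline |
| DAWBA kept, clinic DAWBA reused | Inside the clinic DAWBA, or none | Before the study, age not limited |
| DAWBA dropped after piloting | Stand-alone SDQ | Study baseline |

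Only the second row is defective. The screening questionnaire (Appendix 1) cannot fill it: its SDQ items are an adapted impact supplement about eating difficulties and give no total difficulties score.

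**Consequence in the second row**

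- If the embedded SDQ is paired with the post-treatment SDQ, the interval exceeds the planned 12 weeks by the age of the clinic DAWBA.
- If it is not paired, the post-treatment SDQ has no baseline to be compared with.

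**Illustration of the interval.** Let W be the weeks from clinic DAWBA to study baseline. The protocol gives no value, so 4 to 26 weeks is assumed. The interval is 12 + W and the share before study baseline is W/(12 + W).

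| W (assumed) | Interval (weeks) | Share before study baseline |
| --- | --- | --- |
| 0 (fresh SDQ) | 12 | 0% |
| 4 | 16 | 4/16 = 25% |
| 8 | 20 | 8/20 = 40% |
| 12 | 24 | 12/24 = 50% |
| 26 | 38 | 26/38 = 68% |

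The SDQ would precede the start of treatment by W to W + 1 weeks, against at most 1 week as planned.

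**Illustration of the shift in mean change.** Let m of 10 families have a reused DAWBA, with a mean pre-study drift of d SD. The shift is (m/10) × d. Both m and d are assumed.

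| m of 10 | d = 0.2 | d = 0.5 |
| --- | --- | --- |
| 2 | 0.04 | 0.10 |
| 5 | 0.10 | 0.25 |
| 10 | 0.20 | 0.50 |

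For scale, *Quantitative analysis* calls an effect small from 0.2. The shift could go either way.

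**The case against.** The strongest objection is that the protocol never says in words that the SDQ inside a DAWBA is extracted and paired. *Quantitative analysis* does not name the SDQ, the DAWBA is filed under psychiatric diagnoses, and the SDQ is then listed as post-treatment only. Read literally, that gives no paired SDQ rather than a mismatched one. The *Study summary* points the other way, because it offers the DAWBA and the SDQ as alternatives among the baseline and post-intervention measures. The ambiguity stands, but neither reading gives these families a usable SDQ change over the planned 12 weeks.

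The scope is also narrow, and this stands in full. The gap opens only if the DAWBA survives its pilot and the family's service had used it. The EDE-Q, PEDE-Q, CIA and RCADS are not affected.

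A reader might infer more than the documents support:

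- *That the SDQ is the only general wellbeing outcome.* It is not. The ORS/CORS covers overall wellbeing and the SDQ SxS covers impact, both session by session. Those are analysed visually, so they do not replace a pre-post SDQ, but they are there.
- *That the extra time is time on the waiting list.* Appendices 1 and 5 foresee waiting families, but nothing says how families spent the interval. A family still waiting for assessment would have no assessment DAWBA. Time before the study is as far as the text goes.
- *That reuse will be common.* The *Amendment history* mentions access to existing service data, but gives no frequency and does not name the DAWBA.
- *That 25% to 68% of the SDQ change is bias.* Those figures are shares of elapsed time under an assumed delay, not shares of change.

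**Conclusion.** The point holds in a limited form. While the DAWBA is in use, a family with a reused clinic DAWBA has either an SDQ from before the study, outside the protocol's own timing, or no baseline SDQ to pair. The protocol fixes this as a collection rule, so later analysis cannot repair it.

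The size is unknown, because neither the age of the clinic DAWBAs nor the number of families concerned is given. The intervals of 16 to 38 weeks rest wholly on the assumed delay of 4 to 26 weeks. The shifts of 0.04 to 0.50 SD rest on assumed numbers of families and assumed drift, and also require that the embedded SDQ is the one paired. The description of comorbid diagnoses, which is the DAWBA's stated purpose, is less affected. The change is worth making because it is cheap and cannot be made afterwards.

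**What to change.** - Where a clinic DAWBA is reused, collect a stand-alone SDQ with impact supplement, self- and parent-report, at study baseline. Every family then has an SDQ dated at study baseline, from a newly completed DAWBA or on its own, and the planned interval is 12 weeks for all.
- Use the clinic DAWBA only to describe comorbid diagnoses, and record its date.
- List the SDQ among the baseline and post-intervention measures in *Measures* and in the *Study summary*, stating that a DAWBA newly completed at study baseline supplies the baseline SDQ.

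Asking every family for a separate SDQ is unnecessary: those completing a new DAWBA would answer the same items twice.

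The cost is a few extra minutes for the CYP and the parent in the affected families, against about 45 minutes to repeat the DAWBA, plus a wording change in the protocol.
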